# Effects of physical training on physical and functional fitness, physical activity level, endothelial function, hemodynamic variables, bone metabolism, and quality of life of post-bariatric patients: study protocol for a randomized controlled trial

**DOI:** 10.1186/s13063-022-06677-z

**Published:** 2022-09-02

**Keywords:** Obesity, Bariatric surgery, Muscle mass, Muscle strength, Bone health, Randomized controlled trials

## Abstract

**Background:**

Evidence of the benefits induced from resistance exercise on health markers of post-bariatric patients is limited. The study will investigate the effects of a resistance training (RT) program on muscle mass and strength, bone metabolism biomarkers, bone mineral density (BMD), bone microarchitecture, and endothelial function of patients subjected to Roux-en-Y gastric bypass.

**Methods/design:**

This randomized controlled trial will include 60 post-bariatric patients, physically inactive, aging 18 to 50 years, with a post-surgery period ≥ 12 months. They will be randomly assigned into two groups: (i) the non-exercised control group, which will receive the standard clinical follow-up, or (ii) the intervention group which will consist of RT (60 min/session; 3 times/week, for 6 months). The primary outcomes will include muscle mass and strength, bone metabolism biomarkers, BMD, and bone microarchitecture. The secondary outcomes will be anthropometry, hemodynamic measurements, cardiovascular risk factors, health-related quality of life (QoL), and endothelial function. Outcomes will be assessed by blood biomarkers of bone formation and reabsorption, dual X-ray absorptiometry, repetition maximum and handgrip strength tests, high-resolution peripheral quantitative computed tomography, 36-Item Short-Form Health Survey, venous occlusion plethysmography, and nailfold videocapillaroscopy.

**Discussion:**

It is expected that there are greater benefits from the RT program, possibly improving muscle mass and strength, bone metabolism, density and microarchitecture, QoL, and cardiovascular risk.

**Trial registration:**

ClinicalTrials.gov NCT04193397. Registered on 7 December 2019.

**Supplementary Information:**

The online version contains supplementary material available at 10.1186/s13063-022-06677-z.

## Background

Obesity is a chronic disease associated with multiple comorbidities resulting from the interaction of genetic, metabolic, environmental, and behavioral factors [1]. The prevalence of excess body weight has increased alarmingly over the last few decades. Globally, at least 2.8 million people die from overweight or obesity-related illnesses each year, putting obesity as a significant public health problem [2, 3]. On the other hand, bariatric surgery is an effective therapy to promote significant weight loss compared to clinical treatment, reducing total mortality and improvement or remiting type 2 diabetes, hyperlipidemia, hypertension, and obstructive sleep apnea [4–6].

Despite several clinical benefits, such as reductions in postoperative adverse events and mortality rates, some complications may occur following surgery [7, 8], due to a parallel loss of fat-free mass. Therefore, the bones and muscles may be in part negatively affected.

Unfortunately, there is accumulated evidence demonstrating a reduction in bone mineral density (BMD) [9, 10] after a bariatric procedure. Studies that compared the two most commonly performed techniques [11] showed significantly more bone loss after Roux-en-Y gastric bypass (RYGB) than after sleeve gastrectomy (SG), especially in the lumbar spine, total hip, and femoral neck [9, 10]. This undesired event may result in greater skeletal frailty and risk of fractures [12, 13]. Deleterious effects of bariatric surgery on bone metabolism are related to decreased mechanical stress, calcium and vitamin D malabsorption, secondary hyperparathyroidism, deficiencies of macro- and micro-nutrients, and changes in fat mass and gut hormone secretion [14, 15].

Postoperative muscle loss [16, 17] leads to decreased physical function and resting energy expenditure that contributes to regain of weight [18] and, partly, to relapse of obesity-related comorbidities [6]. It is already known that the advance of age is significantly involved in the loss of muscle mass and strength. Sarcopenia may result from both conditions, leading to difficulties in daily life activities, loss of autonomy, and quality of life (QoL), with higher morbidity and mortality [19].

Strategies to attenuate bone frailty and muscle atrophy in post-bariatric patients are needed, and a resistance training (RT) program can induce positive adaptations in the musculoskeletal system [20, 21], as well as in the stimulus of osteogenic response with preserved BMD in clinical studies [22–24]. In addition, RT contributes to preventing several cardiometabolic risk factors and is considered an independent predictor of all-cause mortality in the general population [25]. However, evidence of the benefits of RT on muscle and bone health in post-bariatric patients is limited. In these patients, additional studies with larger sample sizes, longer exercise interventions, higher volume, and progression overload exercises, and assessment of clinical parameters are necessary to assess the potential of RT on bone health and on fat-free mass integrity [26].

Thus, the present study will investigate the effects of an RT program on muscle mass and strength and on bone metabolism biomarkers, mineral density, and microarchitecture, and endothelial function of patients subjected to RYGB. We hypothesized that the RT program would lead to more remarkable improvement in the assessed outcomes than standard recommendations, as well as in the cardiovascular risk factors and health-related QoL.

## Methods

### Study design

This is a randomized controlled trial, parallel-group, superiority trial with a 1:1 allocation ratio for two arms of treatment. This study protocol will be conducted at the Centro de Pesquisa Clínica Multiusuário (CePeM), Laboratory of Physical Activity and Health Promotion (LABSAU), Laboratory of Clinical and Experimental Research in Vascular Biology (BIOVASC) from the State University of Rio de Janeiro (UERJ), and at the Hospital Universitário Clementino Fraga Filho (HUCFF) from Federal University of Rio de Janeiro (UFRJ) (RJ, Brazil). Patients who were subjected to a RYGB will be recruited at our outpatients’ care unit.

Recruitment, pre-participation screening, allocation, intervention, and data collection will occur between October 2022 and December 2023. We plan that the study will be concluded, and the results will be available for analysis in December 2024. The present study protocol complies with the SPIRIT 2013 recommendations (Standard Protocol Items: Recommendations for International Trials) [27] (see Additional file 1). Figure 1 shows the schedule of enrollment, interventions, and assessments.

**Fig. 1 Fig1:**
[figure not shown]
Schedule of enrollment, interventions, and assessments. −t2, enrolment week; −t1, allocation; t0, pre-intervention; t1, 6 months of intervention; t2, post-intervention

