### Randomization and experimental design

Sixty post-bariatric patients will be randomized through a random code generator software (www.randomization.com) at a ratio of 1:1 into two groups: (a) intervention group—that will perform a supervised RT program for 6 months—or (b) non-exercised control group—that will receive the standard clinical follow-up and shall not change their physical activity behavior. All patients will be followed by a multidisciplinary team (compose of endocrinologists, nutritionists, and physical educators) with expertise in post-bariatric patients, following the clinical practice guidelines [29]. Once the study is completed, for ethical reasons, the exercised control group will be invited to carry out the same RT program. Usual clinical care will be maintained for all patients following completion of the trial at our outpatients’ care unit.

The participants will visit our lab four times for data collection before and after 6 months post-intervention, with at least 24- to 48-h intervals between visits, as shown in Fig. 2. All assessments will be held in the morning between 7 and 11:00 am, in a quiet temperature-controlled environment (21–23 °C). The participants will be instructed to fast for 8 h for blood sample collections and vascular measures (at visit 2). The primary outcomes will be muscle mass and strength, bone metabolism biomarkers, BMD, and bone microarchitecture. The secondary outcomes will be anthropometry, hemodynamic measurement, metabolic/cardiovascular risk factors, health-related QoL, and endothelial function.

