#### One repetition maximum (1RM) test

The dynamic strength maximal assessed by the 1RM test will be used to determine the loads applied during the RT program. After the general warm-up of 5 min, the volunteers will perform a specific warm-up set of 8 repetitions at approximately 50% of the estimated 1RM, followed by another set of 3 repetitions at 70% of the estimated 1RM. The patients will be verbally encouraged to perform 3 to 5 attempts for each exercise with a rest interval of 5 min between them. An interval of 10 min will be allowed before the start of the test for the next exercise. The 1RM will be determined as the higher load achieved.

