#### Handgrip strength test and sarcopenia cutoff points

Isometric maximal handgrip strength will be measured by hand dynamometer TSD121C Hand Dynamometer (Biopac Systems, Inc., CA, USA) with the patients seated in a chair, with elbows flexed and the forearm in supinated position (dominant arm). The patients will perform three attempts of 5 s interspersed with 2-min intervals, and the highest value will be recorded as a result.

Sarcopenia will be detected by cutoff points of low muscle strength and low muscle mass, assessed by the handgrip test and ASM measurement, respectively, defining it as probable or confirmed sarcopenia, according to current consensus [19]. Sarcopenia cutoff points for low muscle strength from Dodds et al. [32] and low muscle mass from Baumgartner et al. [33] will be applied, considering the ratio between ASM by DXA and height squared (ASM index) of 5.45 and 7.26 kg/m^2^ and a handgrip strength of 16 and 27 kg for women and men, respectively.

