#### 36-Item Short-Form Health Survey (SF-36)

Health-related QoL will be assessed using the SF-36 [51]. This tool consists of scores varying from 0 to 100 in eight health domains (physical function, physical role, pain, general health, vitality, social functioning, emotional role, and mental health). A higher score reflects better health perception. Those who grade 50 points or less will indicate poorer health than the reference population [52].

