### Sample size calculation and statistical analysis

In this study, it will be used a similar sample size previously used in a trial which provides 90% detection power between-group differences of BMD, with a significance level of 0.05 [54]. Descriptive analysis will consist of means and SD for continuous variables and percentages for categorical variables. Data normality will be tested by the Shapiro-Wilk test with the results expressed as mean ± SD or percentage, whenever appropriate. Baseline variables will be compared between the groups using either the Student *t*-test or chi-squared test. To compare dependent variables, a two-way ANOVA will be used considering group (intervention and non-exercised control groups) and time points (pre and post-intervention), followed by the Bonferroni post hoc test, in case of significant *F* ratios. An intention-to-treat analysis will be conducted, i.e., all participants, regardless of adherence to the intervention, will be included in the final analysis. No additional analyses are planned for the study. All calculations will be performed using the GraphPad™ software (version 6.0, La Jolla, CA, USA), and the significance level will be set at *P* ≤ 0.05.

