### Masking and blinding

In this study, it will not be possible to blind either patients or investigators who will administer the RT program. On the other hand, a blind researcher will perform the randomization of patients into the study groups. An evaluator and statistician will perform data collection, outcome assessors, and analysis blinded to group allocation.

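### The Fig. 1 legend puts allocation before the pre-intervention assessments, so unblinded patients may know their arm when the 1RM, handgrip and SF-36 baselines are taken

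*Protocol article*

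**What the plan says.** The legend to Fig. 1 gives five time points. Enrolment week is −t2 and allocation is −t1; from allocation onward the order reads "allocation; t0, pre-intervention; t1, 6 months of intervention; t2, post-intervention". Allocation therefore has its own point, ahead of t0.

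The section on randomization and experimental design states: "The participants will visit our lab four times for data collection before and after 6 months post-intervention". The visits are at least 24 to 48 h apart. The statistical section compares the groups with a two-way ANOVA on group and "time points (pre and post-intervention", so the pre-intervention value is the analysed baseline. The same section promises an intention-to-treat analysis that includes every participant regardless of adherence.

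Under Masking and blinding, "it will not be possible to blind either patients or investigators who will administer the RT program". The same section adds: "An evaluator and statistician will perform data collection, outcome assessors, and analysis blinded to group allocation".

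Three of the measures depend on what the patient does or reports:
- 1RM: "The patients will be verbally encouraged to perform 3 to 5 attempts for each exercise".
- Handgrip: "The patients will perform three attempts of 5 s interspersed with 2-min intervals, and the highest value will be recorded as a result".
- Quality of life: "Health-related QoL will be assessed using the SF-36".

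The first two are described under the primary outcomes, the third under the secondary outcomes.

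**The concern.** In an open-label trial, baseline should be recorded before anyone can act on knowledge of the arm. If allocation comes first and is disclosed, a patient can try more or less hard, or rate her health differently, because of the arm she has drawn. The 1RM test is the most exposed, because its result also sets the training loads: a patient who knows she will train has a stake in the result that a control does not. She may also reveal her arm to the evaluator who is encouraging her.

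The pre value is half of the pre/post contrast, so a difference between arms that arises at baseline passes into the estimated change. It would not be the chance imbalance that randomization produces and the standard error allows for.

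There is a second, smaller consequence. Baseline takes several visits. A patient who leaves after allocation but before those visits has been randomized and has no pre value, which a pre/post ANOVA cannot use, although the plan promises to include everyone.

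**Working it through.** **Order of events.** The documents give no figure to reproduce here, so the first check is a reading of the text.

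1. The Fig. 1 legend puts allocation (−t1) before pre-intervention (t0).
2. The statistical section analyses pre- and post-intervention values. Pre-intervention is the label of t0, so t0 is the natural place for the analysed baseline.
3. No section places the pre-intervention visits before randomization or delays disclosure of the arm.
4. Patients are not blinded. The blinded evaluator guards against assessor bias, not against the patient's own effort or self-report.

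The Study design section lists allocation ahead of data collection, but it also lists intervention ahead of data collection, which cannot be true of baseline. I give that list no weight as a chronology.

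**Size, as an illustration.** Inputs:
- n = 30 per arm (60 patients, 1:1, from the article).
- Two-sided 5% test. The article gives the 0.05 level; two-sidedness is assumed.
- Assumed, not in the documents: no true effect; a difference between arms of b = 0.1, 0.2 or 0.3 SD induced at baseline only; pre/post correlation r = 0.7, with 0.5 and 0.9 as a range; equal SD at both times.

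With two time points, the group-by-time test is the comparison of changes. In SD units, the change has standard deviation √(2(1 − r)). At r = 0.7 this is √0.6 = 0.775. The standardized difference is d = b/0.775, and the noncentrality is d × √(n/2) = d × √15 = d × 3.873. Rejection rates come from the noncentral t with 58 degrees of freedom.

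| b (SD) | d at r = 0.7 | Noncentrality | False-positive rate, r = 0.7 | r = 0.5 | r = 0.9 |
|---|---|---|---|---|---|
| 0.1 | 0.129 | 0.50 | 7.8% | 6.7% | 13.6% |
| 0.2 | 0.258 | 1.00 | 16.6% | 11.9% | 39.9% |
| 0.3 | 0.387 | 1.50 | 31.4% | 20.8% | 72.4% |

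Baseline adjustment would only partly help. The bias is then r × b and the residual SD is √(1 − r²) = √0.51 = 0.714. At r = 0.7, b = 0.2 gives d = 0.14/0.714 = 0.196 and a rate of about 12%; b = 0.3 gives d = 0.21/0.714 = 0.294 and about 20%.

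**What the illustration leaves out.** Patients know their arm at post-test under any ordering. If arm knowledge shifts performance at post-test by an amount c in the same direction, the bias in the change is c − b, not −b. With c = b it cancels and the rate returns to 5%. With c = b/2 and b = 0.2, the net shift is 0.1 SD and the rate is 7.8%. The sign is also open: extra effort at baseline in the training arm would bias the change against training.

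**The case against.** The strongest objection is that the legend is only a key to the columns of a figure. The grids of Fig. 1 and Fig. 2 are not available here, and they may show which assessments fall at which point. The legend does not itself say that 1RM, handgrip or SF-36 are done at t0. Drawing the allocation and telling the patient are also separate events, and the article does not say when patients learn their arm; the legend is compatible with disclosure at the first training session. This stands. A reader might infer that patients will know their group at baseline, but the text supports only that they may, since nothing prevents it.

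A reader might also infer that patients could be found ineligible after randomization. The article does not support this. Pre-participation screening is named as a step of its own, and the eligibility criteria are mainly history, diagnoses, medication and excess weight loss. None of them calls for DXA, HR-pQCT, 1RM or handgrip.

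A third tempting reading is that the whole pre/post comparison is compromised. Most primary outcomes (muscle mass and BMD by DXA, HR-pQCT, blood markers) depend little on effort or opinion, and the sample size is tied to BMD. The exposure is confined to the three measures named.

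Finally, the shift sizes are assumed and the percentages presuppose an effect at baseline only. That is correct, and they should be read as a scale and not as an estimate.

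The objections do not remove the order itself. It is stated in the current text, no other passage corrects it, and the blinded evaluator does not address the patient's own behaviour. If the grids do show baseline first, the legend contradicts them and still needs correction.

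**Conclusion.** The point holds in a limited form. As written, the schedule allocates before the pre-intervention point, and neither the order nor any stated delay in disclosure keeps unblinded patients from knowing their arm at baseline. Two primary measures (1RM and handgrip) and one secondary measure (SF-36) are exposed.

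The size and direction of any bias are unknown. Under the assumptions above (shift at baseline only, correlation 0.7, 30 per arm), 0.1 to 0.3 SD corresponds to a false-positive rate of about 8 to 31% in place of 5%, falling towards 5% as a like shift at post-test offsets it. Loss of patients between allocation and baseline is a further cost of this order for the intention-to-treat analysis; the article gives no basis for a number.

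Confidence is moderate, because the figures are not shown and the timing of disclosure is not stated. The change is worth making because it removes an avoidable source of bias that analysis can correct only in part.

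**What to change.** Set the order as enrolment and screening, all pre-intervention visits, allocation, first training session. If allocation must be generated earlier for practical reasons, state that it is not disclosed to the patient or the evaluator until the last pre-intervention assessment has been recorded. Reorder the schedule and the Fig. 1 legend to match. If the figures already place baseline before allocation, correct the legend alone.

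The cost is a re-ordering of existing steps, with no added visits, staff or measurements. The Trial status section says the trial is not yet recruiting, so the change can be made before the first patient is allocated.

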### Recruitment and eligibility criteria

We will approach patients subjected exclusively to RYGB in regular clinical follow-up, aging 18 to 50 years and after at least 12 months from surgery. Our outpatients’ care unit follows at least 180 patients subjected to a bariatric procedure each year. Considering the inclusion and exclusion criteria, we expect to recruit 40 to 60 patients. The exclusion criteria will include regular physical exercise (≥ 3 days/week during 30 min) in the last 6 months; smoking; alcoholism; pregnancy; diagnosis or evidence of any cardiovascular; respiratory, neurological, infectious, endocrine, or musculoskeletal impairments that limit physical exercise; and or being in the use of any hormonal replacement therapy or medications that influence bone metabolism. Those who start some physical exercise program during the study, or with excess weight loss (EWL) < 50% (considered as primary non-responders) [28], or being in the use of drugs that interfere with weight, or who have performed a revisional bariatric surgery will also be excluded.

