### Withdrawals of study and data/safety monitoring plan

The criteria for discontinuation will be (i) participant request, (ii) changes of clinical status during exercise sessions, (iii) absence ≥ 80% of training sessions, and (iv) engagement in another physical exercise program during the study. The principal investigator will oversee and monitor all elements of the trial, with contributions from co-investigators as needed. Patients who present any clinical adverse event during RT sessions will be conducted to the emergency room at our university hospital. Adverse clinical events will be reported to the ethics committee. The Data Monitoring Committee will consist of the principal investigator and co-investigators, who will perform meetings each month throughout the trial period to review data reports on recruitment, screening, baseline and post-interventions assessments, protocol adherence, adverse events, and safety. Since no anticipated problems which could be detrimental to the volunteers are expected in this trial, no interim analysis will be performed.

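### Patients who take up exercise during the study are to be excluded, although the analysis is promised as intention-to-treat for everyone

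*Protocol article*

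**What the plan says.** All places are in the protocol article.

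- **Recruitment and eligibility criteria.** The last sentence opens with "Those who start some physical exercise program during the study", adds patients with insufficient excess weight loss and users of weight-affecting drugs, and closes with those "who have performed a revisional bariatric surgery will also be excluded". Regular exercise in the 6 months before entry is a separate criterion in the preceding sentence.
- **Withdrawals of study and data/safety monitoring plan.** Discontinuation criterion (iv) is "engagement in another physical exercise program during the study". Criterion (iii) is absence from at least "80% of training sessions".
- **Sample size calculation and statistical analysis.** The analysis is by intention to treat: "all participants, regardless of adherence to the intervention, will be included in the final analysis".
- **Randomization and experimental design.** "Sixty post-bariatric patients will be randomized" 1:1. Controls "shall not change their physical activity behavior". Patients in both arms are followed by a team ("compose of endocrinologists, nutritionists, and physical educators").

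**The concern.** Taking up exercise during the study is not a baseline characteristic. Pre-entry exercise already has its own criterion, so this clause adds something only for behaviour after enrolment, and that includes the 6 months after allocation.

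Controls have no training to stop. For them, exclusion or discontinuation can only mean leaving the study, and it falls on exactly those who break the instruction to keep their activity unchanged. Under the intention-to-treat statement these patients are non-adherent and should stay in.

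If the exclusion is followed, the arms compared are no longer the arms randomised. Dropping controls who took up exercise tends to enlarge the apparent training effect, and dropping intervention patients who added other exercise tends to shrink it. A result labelled intention-to-treat would not in itself show which of the two rules had been applied.

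**Working it through.** **The rules side by side, for a control who joins a gym in month 2**

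| Section | Treatment of this patient |
|---|---|
| Recruitment and eligibility criteria | Excluded |
| Withdrawals of study | Discontinued under (iv), on its natural reading |
| Sample size calculation and statistical analysis | Included, as adherence is irrelevant |

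Criterion (iv) stands next to missed training sessions, which can occur only after allocation, so the withdrawal list does cover the post-randomisation period. The first and third rows cannot both be carried out.

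**Inputs.** 60 patients randomised 1:1 give n = 60/2 = 30 per arm. The eligibility section expects 40 to 60 recruits, so the lower case is n = 40/2 = 20. One removal is 1/30 = 3.3% of an arm, or 1/20 = 5.0%. The article gives no uptake rate; the counts and gains below are assumptions.

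**Effect of removal on the estimate.** Let T be the effect of training against no exercise. Suppose c controls each gain a fraction f of T from their own exercise, b intervention patients each gain an extra fraction g, and those removed are otherwise like those who remain.

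- As-randomised effect: T × [1 + (b·g − c·f)/n]
- Effect after removal: T
- Factor = 1 / [1 + (b·g − c·f)/n]

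Example: n = 30, c = 3, f = 0.5, b = 0 gives 1/(1 − 1.5/30) = 1.053.

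| n per arm | Removed | 0.25 | 0.5 | 1 |
|---|---|---|---|---|
| 30 | 1 control | 1.008 | 1.017 | 1.034 |
| 30 | 3 controls | 1.026 | 1.053 | 1.111 |
| 30 | 1 intervention | 0.992 | 0.984 | 0.968 |
| 30 | 3 intervention | 0.976 | 0.952 | 0.909 |
| 20 | 3 controls | 1.039 | 1.081 | 1.176 |

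(Columns are the value of f or g.) With removals in both arms, n = 30 and f = g = 0.5, three controls and one intervention patient give 1.034, three and three give 1.000, and one and three give 0.968.

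**Selection on prognosis.** The table leaves this out. If a proportion p of controls is removed and they differ from the remaining controls by s SD for other reasons, the control mean shifts by p·s. For p = 10% and s = 0.25 to 0.5 the shift is 0.025 to 0.05 SD; for p = 30% it is 0.075 to 0.15 SD.

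**Power.** The planned sample size cannot be reproduced, because the article gives no effect size or SD; the point does not depend on it. For scale, at two-sided 0.05 (sidedness assumed) and 90% power, 30 per arm detects (1.960 + 1.282) × √(2/30) = 0.84 SD. At that difference, removing 10%, 20% or 30% of controls lowers power to about 88%, 86% or 84%. Lost power is the lesser problem.

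**Criterion (iii), only if discontinuation means removal.** It can be met only in the intervention arm. Removing one patient with no gain gives 1/(1 − 1/30) = 1.034. Three sessions a week for 24 weeks is 72 sessions; 0.8 × 72 = 57.6, so 58 must be missed. For 26 weeks, 0.8 × 78 = 62.4, so 63 of 78. With independent attendance, the binomial probability of meeting it (72 / 78 sessions) is 0.524 / 0.500 at 20% average attendance, 0.030 / 0.022 at 30%, and below 0.0001 at 50%.

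**The case against.** The best reply is that leaving the study differs from leaving the analysis. Only the statistics section defines who is analysed, and it is explicit; neither other section says that data are discarded. This has force for the withdrawal criteria. If discontinuation means stopping training, criterion (iii) and intention-to-treat are compatible. It does not settle the eligibility clause, which says excluded and is not reconciled anywhere with a promise to include everyone.

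Three narrower replies soften the point without removing it. Criterion (iv) speaks of another programme, which may suggest the intervention arm; the eligibility clause has no such limit. A patient could enrol, start exercising and be excluded before allocation; but the clause is not confined to that interval. Follow-up of discontinued patients may be described in a fuller protocol; that is accepted, and the concern rests on two stated rules rather than on missing detail.

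It is also fair that the factors in the table, computed with no other selection, describe a change in the question answered (training against no exercise, instead of the comparison as randomised). Bias from prognostic selection would be additional, and its size is unknown.

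**Conclusion.** The concern holds. The article states an exclusion that can be triggered after randomisation, and it conflicts with the article's own intention-to-treat commitment. The conflict between the eligibility and statistics sections carries the point; criterion (iv) supports it, and criterion (iii) matters only if discontinuation means removal, and then rarely.

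The numerical effect is probably modest. With up to three removals from one arm of 30, the estimate changes by a factor between 0.91 and 1.11; with three controls removed from 20, by up to 1.18. Removals in both arms can cancel. These figures rest on assumed counts and gains. Uptake by controls is plausible, since physical educators take part in their follow-up, but no rate is given and the net direction is not certain. This should be corrected, because otherwise the analysed population depends on which section is followed.

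**What to change.** In the eligibility section, restrict the exercise exclusion to the period before randomisation. In the withdrawal section, add that taking up other exercise (iv) is recorded as a protocol deviation, that low attendance (iii) at most ends supervised training, and that every randomised patient is still invited to the 6-month assessments and analysed in the group assigned.

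The cost is one edit, one added sentence and some effort to follow a few patients. If some controls do exercise, the estimated effect may be smaller than under exclusion; that is the intention-to-treat effect the plan says it wants. The sample size does not change.
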